| Tan et al described that with oral 20mg methylprednisolone monotherapy in IGM, 80.7% of patients responded well to steroid treatment. The rationale for a lower starting dose of oral prednisolone of 20mg for Asians is due to higher risk of developing side effects to steroid as compared to their Caucasian counterparts. For this study, 20 mg of prednisolone will be prescribed daily for first 2 weeks, followed by tapering doses of 15mg daily over 2 weeks, then 12.5 mg daily for 2 weeks, proceeding to 10 mg daily for 2 weeks, subsequently taking 7.5mg daily for 2 weeks and lastly 5mg daily for 2 weeks (refer to Figure 2). 20mg of omeprazole is to be taken together with prednisolone. (Refer to Section 8.6 on justification for omeprazole).  Postolva et al described that with oral methotrexate monotherapy (starting dose of 10-15mg/week and increased to 20-25mg/week given orally or subcutaneously) in IGM, 94% had disease improvement^16^. Only oral formulation of methotrexate was chosen in our study to standardize the bioavailability and ease of administration in this trial^17^. In this study, 10mg of methotrexate will be prescribed to be taken once a week for a month and increased to 15mg of methotrexate to be taken once a week for another two months. 5mg of folic acid is to be taken together with methotrexate once a week (Refer to Section 8.6 on justification for folic acid).  *Modification of doses*  Modification of doses may occur during the study period and this will be dependent on patient’s clinical response and the attending doctor’s judgement. Principal Investigator (PI) or Co-Investigators (Co-Is) may increase the methotrexate dosage from 15mg to 20mg and may increase the 5mg folic acid intake up to 6 times a week (except the day of taking methotrexate) to mitigate methotrexate’s side effect, if needed. |  |
| Rationale for Study Population |  |
| The reported incidence of IGM is around 2.4 per 100,000 women aged 20–40 years. The study team will be including women aged 21 to 60 years because IGM often affects women who are young to middle aged. In addition, any women below the age of 21 years are unable to give consent independently in Singapore. |  |
| Rationale for Study Design |  |

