| Figure 1 below shows the study timeline for prednisolone and methrotexate treatment arm.  Figure 2 shows the drug dosage and schedule.  **Figure 1: Study Timeline for Prednisolone and Methotrexate Treatment Arm**   \| **Prednisolone/Methotrexate** \| \| **Study period (1 year)** \| \| \| \| \| \| \| \| --- \| --- \| --- \| --- \| --- \| --- \| --- \| --- \| --- \| \| **Phases** \| \| **Screening** \| **Treatment phase** \| \| \| \| **Follow-up phase** \| \| \| **Time point** \| \| Baseline \| T_0_ \| T_1_ \| T_2_ \| T_3_ \| T_4_ \| T_5_ \| \| Day 0 \| 1^st^  Month \| 2^nd^  Month \| 3^rd^  Month \| 6^th^  Month \| 12^th^  month \| \| Assessment \| Window Period (Day) \|  \| ±7 \| ±14 \| ±14 \| ±14 \| ±14 \| ±30 \| \| Clinical Visit \| X \| X \| X \| X \| X \| X \| X \| \| Blood Test for  FBC/LFT/RP \| X \|  \| X \| X \| X \| X \|  \| \| Blood Test for  Anti-HBc/Anti-HCV/HBsAg/ Serum Beta-HCG pregnancy test ^1^ \| X \|  \|  \|  \|  \|  \|  \| \| Additional Blood for Research \| X \|  \| X \|  \|  \| X \|  \| \| Chest X-Ray ^2^ \| X \|  \|  \|  \|  \|  \|  \| \| Starting Dose \|  \| X \|  \|  \|  \|  \|  \| \| Dose Assessment \|  \|  \| X \| X \| O \|  \|  \| \| Breast Ultrasound \|  \|  \|  \|  \| X \| O \|  \| \| Surveys \|  \| X \|  \|  \|  \|  \| X \|   X= compulsory procedure O=procedure depending on the doctor’s discretion   1. Blood tests (Anti-HBc/Anti-HCV/HBsAg) will be exempted if patient has done the same test within 30 days. 2. Chest X-Ray will be exempted if patient has done the same test within 30 days.   **Figure 2: Flowchart of the treatment schedule for prednisolone and methotrexate during the treatment phase.**  [figure not shown] |  |
| **STUDY DESIGN** |  |
| Summary of Study Design |  |

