| *Screening*  After patient is consented to the study, a baseline blood test (32mls, including pregnancy test, Hepatitis B test, Hepatitis C test, full blood count, liver function test and renal function test) and chest X-Ray will be conducted during the baseline visit to assess for eligibility prior to enrolment to the treatment phase. Additional research blood (14.5mls, 1 tablespoons) will be collected at this baseline visit for research purposes. Patient may be exempted from chest X-Ray and/or blood test if patient has done the same test within 30 days.  Baseline demographics and relevant clinical variables of patients will be collected. The following demographic and clinical variables will be collected: age of presentation, pre-menopausal or post-menopausal status, parity / breastfeeding status, concomitant rheumatic conditions, personal or family history of tuberculosis, smoking or alcohol intake, presenting complaint, unilateral or bilateral involvement, affected quadrant of the breast, duration of symptoms and previous antibiotics prescription for treatment of IGM.  Information on comorbidities will be evaluated to ensure suitability for both treatment arms prior to recruitment. Examples include drug allergies, plans for pregnancy, ongoing infection, previous history of cancer, previous tuberculosis, epilepsy, diabetes, hypertension, kidney, liver, cardiac problems, osteoporosis, glaucoma, peptic ulcers, previous side effects to either prednisolone or methotrexate.  If patient fulfilled all the eligibility criteria after screening assessment, she will be randomised to either of the treatment arm.  If patient did not meet the full eligibility criteria (eg. Pregnant, hepatitis carrier or abnormalities in renal or liver panels), she will not proceed to the treatment phase. The data collected and additional blood samples will be kept for analysis.  *Treatment Phase*  Patient will be scheduled to attend a clinical visit (T_0_) to either breast or rheumatology clinic if she meets all eligibility criteria for the initiation of treatment dose. There will be a window period of ± 7 days for this clinical visit. Patient is required to complete a pre-treatment quality of life online survey (approximately 10-15 minutes).  Patient will be scheduled for blood test (8mls, 0.5 tablespoons) and clinical visits to either breast or rheumatology clinic at the 1^st^ (T_1_), 2^nd^ (T_2_), 3^rd^ (T_3_) and 6^th^ (T_4_) month to assess their signs and symptoms, and drug compliance. There will be a window period of ± 14 days for each of these clinical visits. Additional research blood (14.5mls, 1 tablespoons) will be collected on the 1^st^ (T_1_) and 6^th^ (T_4_) months.  Patients are required to undergo a breast ultrasound to assess for their radiological response during the 3^rd^ (T_3_) clinical visit. A window period of ± 14 days will be applicable. The initial measurement of the breast lesion or mass will be recorded in three dimensions – i.e. anteroposterior, superior-inferior, mediolateral measurements. If complete clinical and radiological complete response has been achieved on the 3^rd^ (T_3_) visit, the doctor will discontinue the drug in a safe manner and no further breast ultrasounds will be required. If the patient’s symptoms or signs have not resolved by the 3^rd^ (T_3_) clinical visit, patient’s drug dosage will be assessed by the rheumatologist and treatment may be continued up to the 6^th^ (T_4_) month period and a repeat breast ultrasound will be required at the 6^th^ (T_4_) month. If symptoms have not resolved by the 6^th^ (T_4_) month of clinical visit, the patient’s drug dosage may be up-titrated or will be given an addition of a second therapy, i.e. combination therapy of steroid and methotrexate may be used. For clinical visits mention above, it will coincides with standard care visit.  During the clinical visits, Tingting Hu et al’s “M- score” will be adopted to grade the severity of the disease. M score is being calculated during clinical visits for IGM patients regardless of trial status for objective follow up. This is a common practice. For this study, the score will be administered by their attending healthcare professional (not limited to breast surgeons, investigators, or breast care nurses).  The M-score will be the sum of the following:  1) Mass score  2) Erythema score  3) Fistula score  4) Pain score  5) Quality-of-life (QoL) score  The scoring criteria were defined as follows:  1) Mass score: 0 for the absence of mass by palpation; 1 for mass ≤3 cm by palpation; 2 for mass >3 cm by palpation.  2) Erythema score: 0 and 2 for the absence and presence of erythema, respectively  3) Fistula: 0 and 2 for the absence and presence of fistula, respectively  4) Pain Score: 0 for Visual Analogue Score (VAS) 0-2; 1 for VAS 3-5; 2 for VAS 6-10  5) QoL score: 0 for absence of effects on QoL; 1 for mild effects on QoL, where the patient does not require medical assistant; 2 for serious effects on QoL, where the patient requires medical assistant  The total M-score ranges between 0 and 10 and serves as a quantitative and objective measurement of the severity of the symptoms.  The primary endpoint will be the clinical complete response (cCR) rate, which is defined as the proportion of patients who have an M-score of ≤ 1 at ≤1 years after treatment.  The secondary endpoints will be as follows:   - - The time to cCR, defined as the median time to cCR post randomisation.   - The treatment failure (TF) rate, defined as the proportion of patients with TF at 1 year post randomisation. The TF status will be defined as follows:     - If the patient has an M-score ≥6 before randomisation, TF is defined as the M-score remaining at ≥6 at 1 month post randomisation.     - If the patient has an M-score between 4 and 5 before randomisation, TF is defined as the M-score remaining at ≥4 and never being lower than 4.     - If the patient has an M-score <4 at baseline but never reaches cCR after randomisation, TF is defined as the M-score being >5 at the follow-up and remaining above 5 for one month. - Relapse rate, which is defined as the proportion of patients who have M-score >4 among the patients who achieved CR.   Throughout the course of the study, there are possible flares and relapse of the disease. Flares will be defined as any increase in M-score or lesion size on ultrasound whilst on therapy. While relapse will be defined as recurrence of symptoms or signs of IGM in the breast after previously experiencing complete resolution following therapy. If relapse occurs, patient will restart the same treatment arm for 6 months.  In the event of flares, blood test (8mls, 0.5 tablespoons) and additional research blood (14.5mls, 1 tablespoons) will be collected and the allocated treatment for the patient will be up-titrated by the doctor. In event of relapse, treatment for the patient will be reinitiated as per the allocated arm.  Additional research blood samples collected during the trial will be used for gene expressing profiling to identify unique patterns of gene expression that can be used to diagnose IGM and predict its treatment response.  Regardless of treatment arm, patient will be monitored by either breast surgeon or rheumatologist. Surgeons will assess for eligibility into trial, clinical reviews, and ultrasound breasts interpretation. Rheumatologists will be monitoring for drug side effects and titration if required. In event of failure of medical therapy, surgeons will have to intervene accordingly for aspiration or surgical drainage. In the event where patients require aspiration or surgical drainage during the study, methotrexate or prednisolone should be continued unless there is evidence of sepsis. The frequency of aspiration or surgical intervention will be recorded as events during the study.  Whenever the disease has been resolved during the study period, the balance medication and/or packaging will be retrieved to do medication accounting and checking for adherence to assigned treatment arm.  If side effects were to develop, doctors will evaluate the severity of the side effects and withdraw the patients from the trial if needed. |  |

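### Section 6.3 orders up-titration for any M-score rise on therapy, even within complete response, where other sections leave it to judgement; separately, the methotrexate schedule is stated in two conflicting ways

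*Protocol*

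**What the plan says.** **Flare rule (6.3, Treatment Phase).** The definition is "Flares will be defined as any increase in M-score or lesion size on ultrasound whilst on therapy". The action is a blood test, a research sample, and an instruction that "the allocated treatment for the patient will be up-titrated by the doctor".

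**Complete response (6.3).** The clinical complete response rate is the "proportion of patients who have an M-score of ≤ 1" within a year of treatment.

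**Dose changes elsewhere.**
- Section 1.2a says doses may be modified during the study and that "this will be dependent on patient’s clinical response and the attending doctor’s judgement". This is not limited to one arm.
- Section 8.3 says methotrexate *may* be raised, depending on response and the doctor's discretion. It says nothing about raising prednisolone.
- Section 6.3 also has rheumatologists titrate where needed. For symptoms still present at month 6 it says the dose *may* be raised, with adding a second drug as the alternative.

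**Methotrexate schedule.** Section 1.2a says "10mg of methotrexate will be prescribed to be taken once a week for a month and increased to 15mg of methotrexate" weekly for two more months, with a permitted increase to 20 mg. Section 5.1 starts at 10 mg. Section 8.3 starts at 15 mg, moves to 20 mg for two months and permits 25 mg.

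**The concern.** The flare definition suits recording and blood sampling, where sensitivity is wanted. Here it also triggers a dose order worded as *will*. A one-point change in a patient whom the protocol counts as a complete responder then calls for more methotrexate or prednisolone. A doctor following 6.3 and a doctor following 1.2a could treat the same patient differently, each within the protocol.

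The flare sentence also does not ask what caused the rise. The quality-of-life item of the M-score is not restricted to breast symptoms, and section 2.4b lists nausea and tiredness for methotrexate and mood changes for prednisolone. If such an effect moved that item from 0 to 1, the literal instruction would be more of the drug that caused it.

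The second defect stands whatever the flare rule says: the sections disagree on the starting dose, the maintenance dose and the highest dose of methotrexate.

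**Working it through.** **1. Can a rise occur within complete response?** Item levels from 6.3: mass 0/1/2, erythema 0/2, fistula 0/2, pain 0/1/2, quality of life 0/1/2.
- Possible single-item rises from M = 0: 2 + 1 + 1 + 2 + 2 = 8.
- Rises ending at M = 1: mass 3 cm or less, pain VAS 3-5, or a mild quality-of-life effect, so 3 of the 8.
- All three stay at or below the threshold of 1. Pain moving from VAS 2 to 3 is enough. This counts score paths; it is not a frequency.

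**2. Can such a patient still be on drug?** Yes. The earliest stop for response is month 3, and it needs both clinical and radiological complete response. A patient at M = 0 at month 1 and M = 1 at month 2 is on therapy, in complete response and in flare by definition.

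**3. Instructions side by side.**

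| Place | Situation | Wording on raising the dose |
|---|---|---|
| 6.3 | Any flare | *will* |
| 6.3 | Symptoms unresolved at month 6 | *may*, or add a second drug |
| 6.3 | Rheumatologist monitoring | where needed |
| 1.2a | Any time, either arm | *may*, by judgement |
| 8.3 | Methotrexate only | *may*, by discretion |

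No section says which governs. A one-point rise within complete response carries a firmer up-titration instruction than disease persisting at month 6.

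**4. Methotrexate, mg/week.**

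| | 1.2a | 5.1 | 8.3 | 8.3 relative to 1.2a |
|---|---|---|---|---|
| Month 1 | 10 | 10 | 15 | 15/10 = +50% |
| Months 2-3 | 15 | refers to Figure 2 | 20 | 20/15 = +33% |
| Highest dose named | 20 | none given | 25 | 25/20 = +25% |

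- Scheduled exposure over three months, as weekly dose times months: 10 + 2 × 15 = 40 under 1.2a and 15 + 2 × 20 = 55 under 8.3. The ratio is 55/40 = 1.375, or 37.5% more under 8.3.
- Named step above schedule: 20 − 15 = 5 mg (5/15 = 33%) under 1.2a, and 25 − 20 = 5 mg (5/20 = 25%) under 8.3.
- Room left under the 1.2a maximum for a patient dosed by 8.3 in months 2-3: 20 − 20 = 0 mg.
- Section 7.1 lists 15 mg/week. That is the second step in 1.2a and the first in 8.3, so it does not settle the matter.

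Figure 2 is not reproduced in the text at hand, so nothing is assumed about it.

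**The case against.** The best defence is that 6.3 should be read as a whole. It has rheumatologists titrate where needed, tells doctors to weigh side effects and withdraw patients if necessary, and introduces flares as flares of the disease. With 1.2a setting discretion for the whole study, the flare sentence may only name who acts. That is probably the intent, and it limits the point: a sensible clinician would use judgement. It does not remove the point. Naming the doctor leaves open at most the size of the increase, not whether to make one, and the context does not require attribution case by case.

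Other replies stand in part. A low escalation threshold is a legitimate clinical choice, and a new small mass may deserve escalation. Discretion will let practice vary between doctors in an open-label trial. Section 8.3 cannot conflict with 6.3 for prednisolone, because it gives only a taper there; that conflict rests on 1.2a. The methotrexate discrepancy is a separate defect and is treated as one here.

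A reader might infer two further conflicts that the protocol does not support.
- **Figure 1.** The month-3 dose assessment is marked O ("O=procedure depending on the doctor’s discretion"), but that concerns a scheduled assessment, not the response to a flare, and months 1 and 2 are marked compulsory.
- **The month-3 rule.** On complete response "the doctor will discontinue the drug in a safe manner and no further breast ultrasounds will be required"; otherwise "drug dosage will be assessed by the rheumatologist and treatment may be continued". This looks at status, while a flare needs an increase. A patient who has come down to M = 1 is not flaring, and assessing the dose does not exclude raising it.

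**Conclusion.** Both parts hold and should be corrected. As worded, 6.3 requires up-titration after a rise as small as 1 point on a 0-10 score, including a 0-to-1 rise within complete response. That conflicts with 1.2a for both drugs, with 8.3 for methotrexate, and with looser wording in 6.3 itself. The conclusion rests on the literal reading; on the generous reading the sentence is merely unclear, and the same edit cures it.

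The methotrexate contradiction needs no interpretation. It is the more serious part because it determines the dose given: 50% higher at the start, 33% higher in months 2-3 and 25% higher at the maximum under 8.3 than under 1.2a.

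A reader might go on to infer that the flare rule biases the comparison of the arms. The protocol gives no basis for that: the rule applies to both arms, and neither the number of patients affected nor any difference between arms can be derived.

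**What to change.** 1. **Methotrexate.** State one schedule and one maximum and use them in 1.2a, 5.1 and 8.3. Which one is for the investigators to choose.
2. **Flare action in 6.3.** Replace the mandatory wording with: treatment may be up-titrated at the doctor's judgement, when the rise is judged due to IGM and not to drug side effects, within the stated methotrexate maximum. Prednisolone increases stay under the judgement described in 1.2a unless the investigators set a limit, since 8.3 names no step or ceiling for that drug.
3. **Precedence.** State that the safety stops in section 3.5 override the flare action.

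Keep the present flare definition for recording and blood sampling. Do not require loss of complete response before escalation; early escalation should remain allowed.

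The cost is a few sentences and one aligned schedule, with no change to visits, sampling or sample size. The small downside is that escalation becomes less automatic and may vary between doctors.

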| This is a prospective pilot randomised trial to study the effectiveness of prednisolone versus methotrexate in achieving clinical or radiological complete response for women with IGM. The study will be conducted in NUH. This study evaluates the effectiveness of each drug in terms of clinical and/or radiological response, time to resolution as well as total number of flares over a period of one year follow-up. This study can potentially identify a more effective treatment with fewer side effects for women with IGM as well as personalize drug choices for patients who are at risk of frequent flares. |  |
| **HYPOTHESIS AND OBJECTIVES** |  |
| Hypothesis |  |
| The hypothesis is that methotrexate has a higher 6-month clinical or radiologically complete response with lesser side effects than prednisolone. The time to clinical or radiological response is shorter in the methotrexate arm compared to prednisolone arm. Relapse and time to first relapse is lower and longer in the methotrexate arm compared to prednisolone arm. |  |
| Primary Objectives |  |
| The primary objective is to evaluate the 1) Proportion of patients who achieved clinical or radiological complete response at 6 months 2) Time to clinical response and time to radiological response, and 3) Proportion of patients with relapse in one year within affected breast between each arm. |  |
| Secondary Objectives |  |
| The secondary objectives include evaluation of:   1. Side effects 2. Frequency of percutaneous or surgical intervention required 3. Potential biomarkers that may predict response to treatment: eg IL-6, CRP and neutrophil to lymphocyte ratio (NLR) 4. Patient reported outcome measures 5. Validate survey instrument for IGM patients |  |
| Potential Risks and benefits |  |
| End Points – Efficacy |  |
| Benefits expected for the patient are the total remission of IGM or reduced relapsed/flare of IGM. |  |
| End Points – Safety |  |

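### The ultrasound part of the flare definition sets no size measure, reference scan or minimum change, so an unchanged lesion has about a 50% chance per comparison of counting as a flare

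*Protocol*

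**What the plan says.** Section 6.3 (Study Visits and Procedures, Treatment Phase) defines the event: "Flares will be defined as any increase in M-score or lesion size on ultrasound whilst on therapy". Lesion size is "recorded in three dimensions – i.e. anteroposterior, superior-inferior, mediolateral measurements". The text does not say how the three figures become one size, which earlier scan the new one is compared with, or how large a rise must be.

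Scans are few:
- Month 3: "Patients are required to undergo a breast ultrasound to assess for their radiological response during the 3^rd^ (T_3_) clinical visit".
- Month 6, if signs or symptoms have not resolved at month 3: "a repeat breast ultrasound will be required at the 6^th^ (T_4_) month". Figure 1 marks this scan as discretionary.
- After complete response at month 3: "the doctor will discontinue the drug in a safe manner and no further breast ultrasounds will be required".
- Figure 1 schedules no ultrasound at baseline, T0, T1 or T2, although section 6.3 speaks of an initial measurement.

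Flares are used in two ways. Section 1.2c says that each drug is evaluated by, among other things, the "total number of flares over a period of one year follow-up". Section 6.3 says that on a flare extra clinical and research blood is taken and "the allocated treatment for the patient will be up-titrated by the doctor".

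**The concern.** Two ultrasound readings of the same lesion rarely agree exactly. A rule that counts any rise turns part of that disagreement into events. This is not detail that can be left wholly to an analysis plan, because the protocol states the rule and it operates during the trial, triggering blood sampling and a treatment change.

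Three things are at stake:
- The ultrasound flares in the one-year count would mix stable and growing lesions.
- Research blood taken at flares, which is meant for gene expression work on treatment response, would carry the same mislabelling.
- The trial is open label (section 8.5) and surgeons interpret the scans (section 6.3). With no tolerance, a trivial reading difference made with the arm known is enough to create an event.

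**Working it through.** The protocol gives no flare rate and no ultrasound measurement error, so it has no figure to reproduce.

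**Inputs from the protocol:** any increase counts; three dimensions are recorded; scans at month 3 and, if unresolved, at month 6; 40 patients.

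**Assumed, not in the protocol:** independent errors with the same distribution at both scans; reading SD of 3% to 15% of each dimension; true size 30 × 25 × 20 mm; readings unrounded, or rounded to 1 mm or 5 mm.

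**1. Unchanged lesion, one size measure, one comparison.** The two readings are exchangeable, so

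P(rise) = (1 − P(tie)) / 2.

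With unrounded readings P(tie) = 0 and P(rise) = 0.50, whatever the size of the error. Ties lower it. One half is therefore the ceiling for a single measure.

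**2. Unchanged lesion, a rise in any of three dimensions counts, independent errors.**

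P = 1 − 0.5³ = 0.875.

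**3. Effect of rounding** (simulation, 400,000 runs; ranges over SD 3% to 15%):

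| Size measure | Unrounded | 1 mm | 5 mm |
|---|---|---|---|
| Longest dimension | 0.50 | 0.35–0.46 | 0.005–0.33 |
| Product of the three | 0.50 | 0.48–0.50 | 0.006–0.46 |
| Any dimension | 0.875 | 0.69–0.84 | 0.006–0.69 |

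If errors in the three dimensions are correlated at 0.5 (SD 10%, 1 mm rounding), the any-dimension figure is 0.70 instead of 0.83.

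**4. Lesion that truly shrank.** With coefficient of variation CV per reading and unrounded values,

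p = Φ( ln(1 − shrinkage) / (√2 × CV) ), and for any of three dimensions 1 − (1 − p)³.

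At CV 10%:
- 10% shrinkage: ln 0.9 / 0.1414 = −0.745, so p = 0.23; any of three = 1 − 0.77³ = 0.54.
- 20% shrinkage: ln 0.8 / 0.1414 = −1.578, so p = 0.06; any of three = 0.16.

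In the simulation with 1 mm rounding and SD 5% to 15%, 30% shrinkage gives at most 0.02 for the longest dimension and 0.12 for any dimension. At 50% shrinkage the probability is about 0.

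**5. Who is exposed.** With no baseline scan scheduled, the only comparison that the schedule secures is month 6 against month 3. It arises only in patients unresolved at month 3, and it counts only if they are still on therapy. That is at most one secured comparison per patient, so at most 40 in the trial. The actual number will be smaller and cannot be derived from the protocol.

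**The case against.** The strongest reply is that little depends on this limb of the definition.

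- Flares are not among the primary or secondary objectives (sections 2.2 and 2.3), the endpoints in section 6.3, or the analyses in section 11.2. The section 6.3 endpoints use M-score thresholds, not the flare label. This stands and limits the weight of the point.
- The M-score is taken at more visits than ultrasound and may supply most flares. This also stands. A reader might infer that the flare count is largely noise, but nothing in the protocol gives the ultrasound share of flares, so that is not shown.
- A reader might take one half as a minimum. It is not: for a single measure it is the maximum (step 1). The 87.5% needs both an any-dimension reading, which the protocol does not state, and independent errors.
- Most lesions should improve: section 1.2a cites 80.7% and 94% doing well on the two drugs, and a clearly shrinking lesion seldom gives a false rise. This is true overall, but it answers only in part. Complete responders at month 3 are not rescanned, so the secured comparison falls on unresolved patients, in whom stable or slowly changing lesions are most plausible.
- Section 1.2a makes dose changes depend on clinical response and the doctor's judgement, and the month-6 text in section 6.3 already permits up-titration when symptoms persist. The added effect of a false label on treatment may therefore be small. The flare sentence is nevertheless unconditional, and the three passages do not agree.

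A reader might also infer a direction of bias. False flares spread evenly over comparisons dilute a difference, whereas the arm with more unresolved patients has more scan pairs and so more chances of a false flare. The protocol does not show which effect is larger.

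**Conclusion.** The concern holds in a limited form. As written, the ultrasound component cannot separate stable from growing lesions. An unchanged lesion is called a flare about 50% of the time per comparison, less when rounded readings tie and up to 87.5% if any of three independent dimensions counts. The 50% rests only on equal error distributions at the two scans and unrounded readings. The figures for rounding and shrinkage rest on assumed error sizes.

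The effect is confined mainly to patients unresolved at month 3 who are rescanned at month 6 on therapy. Its share of all flares, and its net effect on the difference between arms, cannot be calculated from the protocol. Because flares are named as an outcome only in the design rationale, this is a point to consider, not one that undermines the trial's listed endpoints.

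**What to change.** For the counted flare outcome, amend section 6.3 to:

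1. Name one size measure, for example the product of the three recorded dimensions.
2. Name one reference scan, and reconcile the initial measurement with Figure 1, which shows no scan before month 3.
3. Count an ultrasound flare only when the increase exceeds a tolerance fixed before any outcome comparison. The protocol plans no repeat readings, so the tolerance has to be a stated judgement and not an estimate from trial data. It must be set on the scale of the chosen measure: with independent errors of 10% per dimension, the product varies by about √3 × 10% = 17%.
4. Report M-score flares and ultrasound flares separately.

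As an illustration of what a tolerance achieves, not a proposed value: if a rise counted only at 20% or more in the longest dimension, P = 1 − Φ(0.20 / (SD × √(1 + 1.2²))). An unchanged lesion would then be counted in about 0.5%, 10% and 20% of comparisons at reading SDs of 5%, 10% and 15%.

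Separately, the flare sentence that makes up-titration automatic must be reconciled with section 1.2a and with the permissive month-6 wording in section 6.3. No treatment rule is proposed here.

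The cost is a wording change, with no added visit or scan. The downside is small: a true increase below the tolerance is not counted at that scan.
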